#### Cardiac adverse events

Ninety-day incidence of cardiac device infections will be measured using the semi-automated measurement tool adapted for near-real time surveillance. Effectiveness of the tool based on champion feedback will be included in trial results.

### Data analysis

#### Analysis of quantitative data elements

The primary outcome measure is the *adoption* of guideline-based pre-procedure prophylaxis and *de-adoption* of guideline-discordant post-procedure prophylaxis, defined as a change in the proportion of procedures with guideline-concordant antimicrobial use practices. This will be assessed by using an interrupted time-series analysis at the three study sites with comparison of proportions, accounting for facility and random fixed-effects. A regression model adjusted for patient and facility characteristics will then be used to estimate the impact of fidelity of accessing reports on adoption of guideline-based practices.

The quantitative effectiveness (primary outcome) of the implementation strategy will be measured through the change in the adoption of evidence-based antimicrobial use at the three sites. This will be calculated as the change in proportion of cases *without* post-procedural antimicrobials lasting for >24 h after skin closure, as measured by the automated algorithm. The analysis will use a generalized linear mixed model to estimate the probability of pre-and post-implementation antimicrobial use, accounting for facility-level correlation as a random effect. We will also explore the influence of calendar time in the Stepped-Wedge Design using models described by Nickless et al. [35].

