#### Clinical outcomes are secondary in this hybrid type III trial

Clinical outcomes reported are selected to assess the impact of improving adoption of guideline-concordant antimicrobial prophylaxis on important clinical outcomes theoretically linked to appropriate application of peri-operative prophylaxis, specifically, CIED infections (impacted by appropriate pre-procedural antimicrobial use), and AKI and *C. difficile infections* (both impacted by appropriate early discontinuation of antimicrobial use). These data will be extracted from the VA EHR using the automated algorithm and CIED infections will be validated by manual review at the main study site. Similar to the analysis of the implementation outcomes, incidence of key clinical outcomes will be measured pre- and post-implementation at each of the three sites, applying a generalized linear mixed model with allowance for a facility random effect. We will again explore the influence of calendar time in the stepped-wedge design using models described by Nickless et al. [35].

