#### Discussion and limitations of the approach

This study will focus on de-implementing an intervention with a strong evidence basis against its use, as well as a guideline-based recommendation supporting the practice change. This is both a strength and a limitation of the study. Prior research and the formative interviews suggest that the strength of the knowledge base is a major driver of success [11]. This factor is likely to increase the probability of this project’s success, however, will limit generalizability to settings where the evidence base and the clinical guidelines are less clear, particularly to interventions with a mixed or untested evidence base. In addition, this study is targeting a relatively simple clinical intervention—short-term prescribing of a single medication; simple and short-term interventions are generally viewed as easier to de-implement than more complex interventions. The use of external facilitation and a semi-automated surveillance system reduce the workload burden on intervention sites; limiting personnel requirements at the participating sites is another factor that favors success of this specific project but may limit generalizability to interventions that would require facilities to hire additional staff to carry out the proposed interventions. In addition, this study will be conducted at three large volume VA medical centers. Findings may not be generalizable to other VA medical centers or to non-VA medical systems. Finally, this study uses a quasi-experimental, rather than randomized, design. This will impact our ability to fully attribute causality to the multifaceted implementation bundle.

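### Patient-level adjustment is specified only for the fidelity regression; the primary and clinical-outcome models name facility effects only, so a case-mix change at roll-out could be read as effect

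*Protocol article*

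**What the plan says.** The Protocol article describes four quantitative analyses under Data analysis.

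- **Primary outcome, first description** (Analysis of quantitative data elements): an "interrupted time-series analysis at the three study sites with comparison of proportions, accounting for facility and random fixed-effects".
- **Fidelity** (same section): "A regression model adjusted for patient and facility characteristics will then be used to estimate the impact of fidelity" of report access on adoption.
- **Primary outcome, second description** (same section): a generalized linear mixed model to "estimate the probability of pre-and post-implementation antimicrobial use, accounting for facility-level correlation as a random effect".
- **Clinical outcomes** (Clinical outcomes are secondary in this hybrid type III trial): "Similar to the analysis of the implementation outcomes, incidence of key clinical outcomes will be measured pre- and post-implementation", "applying a generalized linear mixed model with allowance for a facility random effect".

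On time, the primary-outcome text says "We will also explore the influence of calendar time in the Stepped-Wedge Design", and the clinical-outcome text repeats the intention. The limitations section states that "this study uses a quasi-experimental, rather than randomized, design" and accepts that causal attribution is weakened.

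**The concern.** The pre- and post-implementation groups consist of different procedures in different patients at three sites that were not randomised. If the mix of patients or procedures changes within a site between the two phases, and that mix is related to prolonged prophylaxis or to the clinical events, the pre/post contrast contains the change in mix as well as any change in practice. It could inflate the apparent effect or hide a real one.

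A facility random effect takes up stable differences between sites. It does nothing about change over time within a site. The article names the usual remedy, adjustment for patient characteristics, but attaches it to the fidelity regression and not to the models that carry the trial's main conclusions. That is a statement of model form, which is more than an unlisted set of covariates.

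**Working it through.** **1. The four analyses side by side**

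| Analysis | Facility term | Patient terms | Calendar time |
|---|---|---|---|
| Interrupted time series (primary) | yes | none named | trend terms not described |
| Fidelity regression | yes | yes | not mentioned |
| Mixed model (primary) | random effect | none named | to be explored |
| Mixed model (clinical) | random effect | none named | to be explored |

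**2. Reproducing the plan's power figure, to see which model it assumes**

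Inputs from Power calculations: 135 cases per site, before and after combined; discordant use 0.50 to 0.35; coefficient of variation 0.2; alpha 0.05; the Hussey and Hughes method. Assumed here: two-sided test, 3 sites by 4 periods, and 135/4 = 33.75 cases per cell.

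- Between-site SD: 0.2 × 0.50 = 0.10.
- Variance per case at the average rate 0.425: 0.425 × 0.575 = 0.244.
- Without period effects, generalised least squares gives SE = 0.053. Power = Φ(0.15/0.053 − 1.96) = Φ(0.87) = 80.8%. The plan states 80%.
- With period effects, SE = 0.0892. Power = Φ(0.15/0.0892 − 1.96) = Φ(−0.28) = 39% (38% to 43% across variants of the variance assumptions).

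Under this layout the stated power matches a model without calendar time. This fits the wording, in which calendar time is exploratory.

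**3. Size of a case-mix artefact**

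The documents give no patient characteristic, prevalence or association, so every input here is assumed. With no change in practice:

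spurious change = (shift in share of a characteristic) × (risk difference it carries)

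| Shift in share | RD 10 points | RD 20 points | RD 30 points |
|---|---|---|---|
| 5 points | 0.5 | 1.0 | 1.5 |
| 10 points | 1.0 | 2.0 | 3.0 |
| 20 points | 2.0 | 4.0 | 6.0 |

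The results are in percentage points. Against the 15-point target the range is 0.5/15 = 3% to 6/15 = 40%.

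**4. Effect on the test if the shift occurs at every site's crossover**

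Type I error = Φ(−1.96 + b/SE) + Φ(−1.96 − b/SE), with SE = 0.053 and b the spurious change:

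- b = 0.005: 5.1%
- b = 0.03: 8.7%
- b = 0.06: 20.5%

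With period effects (SE = 0.0892), b = 0.06 gives 10.3%. The figure is lower because the SE is larger; the bias is the same.

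**5. Which shifts survive which model**

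The shifts below were passed through the same estimator, for total shifts of 2, 4 and 6 points.

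| Pattern of shift | No period effects | Fixed period effects |
|---|---|---|
| Common to all sites, linear in time | 1.3, 2.6, 3.9 points | 0 |
| At each site's own crossover | 2, 4, 6 points | 2, 4, 6 points |
| Gradual drift at site 1 only | 0.45, 0.9, 1.3 points | 0.05, 0.09, 0.14 points |

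The estimator is linear, so the contributions of the three sites add up to the whole. A step at the crossover of one site alone therefore contributes on average a third: 6/3 = 2 points at the top of the range.

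**6. Events available for adjusting the clinical model**

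0.02 × 2,100 = 42 infections at the rate and number of procedures given under Impact on CIED infections outcomes.

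**The case against.** The strongest reply is that the article is a condensed account and nowhere says the main models are unadjusted; covariate lists usually sit in an analysis plan, which is not shown. That stands against a reader who infers that the authors have ruled adjustment out. It does not remove the point, because the article does assign patient adjustment, and assigns it to one model.

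Second, the plan has other defences. The interrupted time series could absorb gradual drift if it models trend. The stepped-wedge layout sets waiting sites beside active ones, and the calendar-time models, once fitted, remove drift common to all sites entirely (step 5). This stands, and it narrows the concern to site-specific changes and changes at crossover. But trend terms are not described, and calendar time is only to be explored.

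Third, the article attributes prolonged prophylaxis largely to local habit and a perceived standard of care. If prescribing is that uniform within a facility, patient mix explains little of it, and the low end of the range is the relevant one. That is a fair reason not to assume a large bias in the primary outcome. It has less force for kidney injury and infection, which are patient-level events.

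Two stronger readings are tempting. One is that case-mix shift is being counted as effect. No shift is documented, and the pandemic is mentioned only in connection with virtual or in-person contact. The other is that the needed covariates are already extracted. The variables listed in Table 1 are prophylaxis, infection, kidney injury and *C. difficile* measures. That patient characteristics will be available is an inference from the fidelity regression.

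**Conclusion.** The point holds in a limited form. As written, the models for the primary and clinical outcomes contain no named protection against a change in patient mix within a site, while the fidelity regression does. A site-specific shift, or one that coincides with crossover, could be attributed to the bundle. Common drift is removed only if calendar time is in the model, or if the time series models it as trend.

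The range of 0.5 to 6 points is an illustration. It rests on the assumed shifts and risk differences, and on the shift occurring at every site's crossover. The low end is negligible and the high end is material. The general caveat about causality in the limitations section is honest, but it does not replace an adjustment that the plan already foresees for another analysis. This is a recommended change and does not invalidate the design.

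**What to change.** - In the primary mixed model, enter as fixed covariates a short pre-specified set of the patient and procedure characteristics needed for the fidelity regression, all measured before the prophylaxis decision. Device or procedure type, age, baseline kidney function and diabetes are examples only; the article names none.
- Report the adjusted marginal risk difference beside the unadjusted one, so that readers can see how much of the change depends on patient mix.
- State whether calendar time enters the main model or remains a sensitivity analysis, since that decides whether common drift is removed.
- For the rare clinical outcomes, limit adjustment to a few covariates chosen in advance, given about 42 expected infections.

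The cost is a change of analysis wording, slightly more analysis work and a rule for missing covariates. No new data collection should be needed if the characteristics for the fidelity regression are obtained as planned; the sponsor should confirm this.

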## Introduction

In the USA, more than 300,000 cardiovascular implantable electronic devices (CIEDs), such as pacemakers and defibrillators, are placed annually [1, 2]. Guideline-driven antimicrobial prophylaxis reduces CIED infections and improves outcomes. Clinical guidelines emphasize the importance of timing and duration of peri-procedural prophylaxis to achieve optimal benefit [3, 4]. To reduce infections, antimicrobials must be given before incision. Discontinuation within 24 h after skin closure is recommended because prolonged antimicrobials cause harm, including acute kidney injuries (AKI) and *Clostridioides difficile* infections, but do not reduce infections [3, 5, 6, 7].

Guidelines about timing and duration of antimicrobial prophylaxis are often not adhered to, and excessive antimicrobials are prescribed after more than 50% of CIED procedures, leading to patient harms [8]. Formative evaluations with electrophysiologists who perform these procedures concluded that these clinicians are highly motivated to prevent infections but that they overestimate benefits of prolonged antimicrobial use and underestimate harms, in part due to lack of feedback about the adverse consequences that result from prolonged antimicrobial prophylaxis [9].

De-implementation is recognized as an important area of research that can lead to reductions in unnecessary, wasteful, or harmful clinical practices, such as excess antimicrobial use following CIED procedures; however, investigations into approaches that lead to successful de-implementation are limited [10]. Theories suggest that factors that may have a particularly strong influence on de-implementation include strength of the underlying evidence, the complexity of the intervention, and patient and provider anxiety and fear about changing an established practice [11]. Because de-implementation is a distinct process [12], tailored strategies that recognize de-implementation specific barriers may be necessary to achieve successful discontinuation [11].

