#### Quality monitoring/audit and feedback reports

Reports created by the primary site will be provided to local champions (i.e., infectious diseases/infection control team members) via a secured data transfer method. Reports will include data such as (1) rates of appropriate pre-procedural antimicrobial use, (2) CIED infection events and rates, (3) antimicrobial-associated adverse events and rates (e.g., *C. difficile* infections, AKIs), (4) rates of post-procedural antimicrobial use benchmarked to high-performing facilities and providers, and (5) CIED infection rates benchmarked to other facilities. Rates of guideline-concordant antimicrobial use are included to reinforce positive behavior (learning), and rates of guideline-discordant use and benchmarking are included to promote unlearning and de-adoption. The reports will give the sites information about application of guideline-concordant practices at other high-performing facilities to ensure providers that they are not “outliers,” a barrier identified in formative evaluations. Rates of infections and adverse events are included to provide reassurance that the practice change is improving clinical outcomes by reducing non-cardiac adverse events and not worsening CIED infection rates. Adverse events that arise from inappropriate antimicrobial use are included to highlight tangible harms associated with lack of guideline compliance and to promote *unlearning*.

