#### Local adaptations to reports to optimize performance and local utility

Facilities will be provided with preliminary audit and feedback reports, which will include CIED infection rates calculated using the electronic data extraction tool followed by manual validation, rates of guideline-concordant pre-procedural antimicrobial use and guideline-discordant post-procedural antimicrobial use, AKIs and *C. difficile* infections, and benchmarking about post-procedural antimicrobial use to high-performing sites. Local feedback will be used to make adaptations, such as the preferred method and timing for receiving the report, the preferred method of data presentation and comparison (graphs, quantitative measures), and the degree to which individualized versus facility-level data are included. Sites will be asked to provide input about the accuracy of the reports (e.g., were there infection cases identified by clinical operations that were not detected?), the utility of the reports (e.g., were the cases known to the infectious diseases and infection control services) and about how to make the reports user-friendly. Input from the participating sites will be incorporated and reports will be revised based on their feedback. If necessary, based on feedback about accuracy of infection detection, adjustments to the electronic algorithm will be made to improve performance. Investigators will track all feedback, including about accuracy and changes to the electronic detection tool, in the final report of findings.

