#### Identification and engagement of key stakeholder groups

Several key stakeholder groups have been identified and will be engaged during the project. These include cardiology stakeholders (e.g., electrophysiologists and other electrophysiology team members) and infectious diseases and infection control stakeholders (e.g., infectious diseases physicians and pharmacists, infection control specialists). *Electrophysiologists* and other cardiology stakeholders are targeted by the educational and feedback components of the strategy. *Infectious diseases/infection control specialists* are the local champions and internal facilitators who will act upon the reports.

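### The primary model allows for facility only, so a change in which electrophysiologists operate at a site could be counted as de-implementation or could hide it

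*Protocol article*

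**What the plan says.** Under Analysis of quantitative data elements, the protocol article measures the primary outcome as the change in the proportion of procedures without antimicrobials beyond 24 hours after skin closure. The model is a generalized linear mixed model "accounting for facility-level correlation as a random effect". The other analyses in that section also stop at the facility:

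- The interrupted time-series analysis is described as "accounting for facility and random fixed-effects".
- The fidelity analysis has no provider term: "A regression model adjusted for patient and facility characteristics will then be used to estimate the impact of fidelity".
- Calendar time is exploratory: "We will also explore the influence of calendar time in the Stepped-Wedge Design".

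The clinical outcomes use the same facility random effect.

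Elsewhere the article treats the individual prescriber as the person whose practice must change. The Introduction reports "Formative evaluations with electrophysiologists who perform these procedures concluded" that these clinicians overestimate benefit and underestimate harm. Under Identification and engagement of key stakeholder groups, electrophysiologists "are targeted by the educational and feedback components of the strategy". The reports include "rates of post-procedural antimicrobial use benchmarked to high-performing facilities and providers", and sites may choose "the degree to which individualized versus facility-level data are included".

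**The concern.** The theory under test is that prescribers unlearn a habit once they see its harms. A site's discordant rate can fall for two different reasons: the same operators change what they do, or different operators do the procedures. A model whose only level is the facility cannot tell these apart. Benchmarking against providers implies that the study team expects prescribers to differ and can attribute procedures to them.

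The analyses described would not remove the problem. Patient adjustment is stated only for the fidelity model and concerns patients, not operators. A staffing change at one site is not a calendar trend shared by all sites. With only three sites, such changes do not average out well. At stake are the attribution of an observed change to the strategy and the width of its confidence interval.

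**Working it through.** **Inputs from the article (Power calculations):** three sites; 135 cases per site, before and after combined; discordant use falling from 0.50 to 0.35 at each site; alpha 0.05 (taken as two-sided); coefficient of variation 0.2; about 2100 procedures in all, so 2100/3 = 700 per site.

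**Assumed, because the article gives none:** the number of operators k at a site, their spread, and any replacement.

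**1. The plan's own figure.** I used the Hussey and Hughes variance with an assumed layout of 3 sites by 4 periods, 135/4 = 33.75 cases per cell, between-facility SD 0.2 × 0.50 = 0.10, and no period effects. The standard error is 0.0530 and power is Φ(0.15/0.0530 − 1.96) = Φ(0.87) = 0.81. The stated 80% is reproduced. (It needs period effects to be left out, which is a separate matter.) The calculation has binomial and between-facility variation, and nothing for operators.

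**2. One replacement, nobody changing practice.** Four equal-volume operators at 80, 60, 40 and 20% give (80+60+40+20)/4 = 50%. Replace the 80% operator by one at 20%: (20+60+40+20)/4 = 35%. The site moves 15 points. With equal site weights the three-site average moves 15/3 = 5 points.

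In general the site shift is (pH − pL)/k, and the average shift is one third of that:

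| k | 0.8 to 0.2: site / average | 0.6 to 0.4: site / average |
|---|---|---|
| 3 | 0.200 / 0.067 | 0.067 / 0.022 |
| 4 | 0.150 / 0.050 | 0.050 / 0.017 |
| 5 | 0.120 / 0.040 | 0.040 / 0.013 |
| 8 | 0.075 / 0.025 | 0.025 / 0.008 |

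A shift in case shares does the same without anyone leaving. Moving 0.15/0.60 = 25% of a site's volume from an 80% to a 20% operator gives 15 points at that site. Between a 60% and a 40% operator it takes 0.15/0.20 = 75%.

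**3. Random replacement.** Draw operator rates on the logit scale with SD 1 and replace one of k at random. The site shift then has SD 9.8, 7.4 and 5.9 points for k = 3, 4 and 5. For a replacement at one site only, the average has one third of that: 3.3, 2.5 and 2.0 points. At logit SD 0.5 the site figures are 5.6, 4.2 and 3.3 points.

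**4. Effect on the interval.** Take a simple pre/post comparison with half the cases in each period, k = 5, operator SD 0.2 on the proportion scale, and one replacement per site at rollout.

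- Binomial variance of the three-site difference at 135 per site: (2 × 0.25/67.5)/3 = 0.00247, SE 0.0497.
- Added operator variance: (2 × 0.2²/5²)/3 = 0.00107.
- True SE: √(0.00247 + 0.00107) = 0.0595.
- False-positive rate: 2[1 − Φ(1.96 × 0.0497/0.0595)] = 2[1 − Φ(1.64)] ≈ 0.10.

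Simulation of the same setting gave 0.105. The fuller simulated grid, with no true change and a nominal rate of 0.05, is:

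| Cases per site | k | Operator SD 0.1 / 0.2 / 0.3 |
|---|---|---|
| 135 | 3 | 0.087 / 0.187 / 0.295 |
| 135 | 5 | 0.063 / 0.105 / 0.150 |
| 135 | 8 | 0.057 / 0.071 / 0.093 |
| 700 | 3 | 0.23 / 0.47 / 0.60 |
| 700 | 5 | 0.12 / 0.28 / 0.40 |
| 700 | 8 | 0.08 / 0.15 / 0.23 |

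With no replacement and stable case shares the rate stayed at 0.047 to 0.056. About half of the false positives pointed to improvement and half to worsening. More procedures make the inflation worse, because binomial error shrinks and operator variation does not.

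**5. Milder scenarios and the remedy.** A separate linear mixed-model check, with its own assumed counts and spread, gave facility-only rates of about 0.05 to 0.16 at 135 per site and 0.10 to 0.45 at 700 with a replacement at every site. With a replacement at one site only they were 0.04 to 0.07 and 0.07 to 0.27. Adding an operator effect, its variance taken as known, brought them to about 0.05 or below, with an equal or tighter estimate.

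**The case against.** The strongest reply is that the facility is the right level. Rollout is by site, reports go to local champions, and champions can rewrite local protocols. A new operator who follows a revised protocol is part of the intended effect. This stands: the facility term must stay, and an analysis of continuing operators cannot replace the primary one.

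It is also fair that every driver of the size is assumed. The article does not say that sites have few electrophysiologists, that any will leave, or how far they differ. Its Table 1 and its section on blended facilitation describe practice as shaped by local culture and norms, which would narrow operator differences. The calculations put the replacement at crossover, which is the worst timing; crossovers are staggered, and a change at another time would be diluted.

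A reader might infer that staff turnover will be scored as adoption, or that one departure could reverse the trial's result. The documents support neither. Random turnover is as likely to hide an effect as to create one. The Power section assumes its 15-point change at each site, so 15 points at one site is about 5 on average, one third of the target.

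The article also plans interviews that ask about unlearning, and its limitations section concedes that causality cannot be fully attributed. Neither addresses operator mix in the estimate or its interval. Nor is this just detail left to an analysis plan: the article states the correlation structure and fixes it at one level.

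**Conclusion.** The concern holds in conditional form. As stated, the primary model does not protect against a change in operator mix. Such a change could be read as de-implementation or could conceal it, and the facility-only interval would then be too narrow as a statement about the strategy.

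Two conditions are needed: operators within a site differ, and their presence or case shares change between periods. The documents establish neither. Under the assumptions shown, one marked replacement at one site moves the average by 2.5 to 6.7 points (k = 8 to 3, 80% to 20%), and a 60%-to-40% replacement by about 1 to 2 points. False-positive rates range from essentially nominal to several times nominal, and the highest require a replacement at every site, three operators and wide spread. This is mainly unmodelled variance, not a bias in a known direction.

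**What to change.** Where the operator identifier can be obtained from the health record:

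1. Keep the facility term and add an electrophysiologist random effect nested in facility to the primary generalized linear mixed model.
2. Report operator mix (procedures per operator) by site and by pre- and post-implementation period.
3. Add a supporting analysis, not a replacement, restricted to operators with procedures both before and after implementation.

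Keep the facility-level change in proportion as the primary estimand.

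The cost is one model term, one table and one supporting analysis, with no extra patients. Provider benchmarking suggests the identifier exists, but the extraction list in Table 1 of the article does not name it, so this must be confirmed. A random operator effect also uses differences between operators, so it removes a change in mix only in part, and its variance must be estimated from however many operators there are. The supporting analysis drops operators seen in one period only, so its interval may be wider, and it leaves out the effect of a changed site protocol on new operators. If staffing proves stable, these additions show it and strengthen the claim of unlearning.

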## Study design and methods

### Trial design

This clinical trial uses a hybrid type III effectiveness-implementation stepped-wedge design at three high-volume and high-complexity VA medical centers (Table 2) [22]. The primary endpoint evaluated in hybrid type III studies relates to the effectiveness of the implementation strategy or strategies; clinical outcomes are secondary [22]. Increased uptake of guideline-based recommendations is expected to translate into improved clinical outcomes; however, the study is primarily powered to assess the effectiveness of the multi-faceted intervention for promoting adoption of guideline-concordant antimicrobial use practices.

**Table 2 Tab2:** Stepped-wedge design of the hybrid III implementation/effectiveness trial

Site	0–6 Months	6–12	12–15	15–18	18–21	21–24	24–30	30–46	36–48
**1**	Development of educational materials, IRB submission, data collection, initial report development	Education	Adaptation, facilitation	Wash-in	Reports provided	Reports provided	Reports provided	Reports provided	Qualitative data and quantitative collection and analysis
**2**			Education	Adaptation, facilitation	Wash-in	Reports provided	Reports provided	Reports provided	
**3**				Education	Adaptation, facilitation	Wash-in	Reports provided	Reports provided	

The stepped-wedge design is chosen for several reasons. Stepped-wedge designs have been used successfully in implementation research trials [23, 24], including trials designed to improve infection prevention and patient safety practices [25]. The stepped-wedge design staggers the introduction of the implementation strategy. Because of this, stepped-wedge trials are susceptible to changes based on secular trends; however, by temporally aligning sites awaiting implementation with sites undergoing active implementation, stepped-wedge trials have the advantage of more fully controlling for practice trends unrelated to the implementation strategy than alternative designs, such as parallel-groups randomized controlled trials [26].

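### The pre/post GLMM tied to primary effectiveness names only a facility random effect and leaves calendar time to exploration, so a secular trend would bias the estimate in either direction; the stated power fits a model without time.

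*Protocol article*

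**What the plan says.** In *Analysis of quantitative data elements*, the first paragraph says the primary outcome will be assessed by an "interrupted time-series analysis at the three study sites with comparison of proportions, accounting for facility and random fixed-effects". The second paragraph then ties quantitative effectiveness, labelled there as the primary outcome, to a "generalized linear mixed model to estimate the probability of pre-and post-implementation antimicrobial use, accounting for facility-level correlation as a random effect". It closes with "We will also explore the influence of calendar time in the Stepped-Wedge Design", using published models. The article does not say which of the two analyses decides.

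For the clinical outcomes, the article plans a pre/post comparison "applying a generalized linear mixed model with allowance for a facility random effect". Calendar time is again only explored, and no interrupted time series is named.

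*Trial design* concedes that "stepped-wedge trials are susceptible to changes based on secular trends" and then defends the design because sites still waiting are aligned in time with sites already active. The limitations section says that the study is quasi-experimental and not randomised.

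**The concern.** In a stepped wedge every site moves from control to intervention as time passes, so exposure and calendar time are confounded by construction. The alignment of waiting and active sites controls secular trend only if the model compares them at the same time, which needs a time term. A pre/post model with a facility effect compares each site's later cases with its own earlier ones and takes up whatever else changed. Because allocation is not randomised, the order of roll-out gives no separate protection.

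The estimate, confidence interval and p-value for adoption are at stake. A background fall in prolonged prophylaxis would be credited to the implementation bundle, and a background rise would hide a real effect. The same holds for the clinical outcomes.

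**Working it through.** **Inputs from the article.** Three sites; 135 cases per site, before and after combined; discordant use 0.50 to 0.35; alpha 0.05; 80% power; coefficient of variation 0.2; the Hussey-Hughes procedure (*Power calculations*). Wash-in is excluded (*Phase IV*). Volume exceeds 100 procedures per year per site, so 300 or more over 36 months; N of about 2,100 is given under secondary power, or 700 per site. The schedule is Table 2.

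**Assumptions.** Two-sided alpha; cases spread evenly over months 0 to 36; the Table 2 column printed 30–46 read as 30–36; education and adaptation months counted as pre; a linear background trend of assumed size.

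**Step 1: reproduce the stated power.** Hussey-Hughes variance on site-period means, with an assumed four-period wedge, 135/4 = 33.75 cases per cell, and between-site SD 0.2 × 0.50 = 0.10. Case variance is 0.25 at the baseline rate, or 0.425 × 0.575 = 0.244 at the mean rate. Power = Φ(0.15/SE − 1.96).

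- Without period effects: SE 0.0536 or 0.0530, power 0.799 or 0.808. The 80% reproduces.
- With period effects: SE 0.0901 or 0.0892, power 0.384 or 0.390. About 396 cases per site would be needed for 80%.

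Layouts with 5, 6 or 8 periods gave 0.80 or more without period effects and 0.37 or less with them (two-sided). Reading 135 as cases per site *and period* gives about 0.90 with period effects, which also does not match.

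**Step 2: bias on Table 2.** With wash-in removed, mean pre and post dates in months are 7.5 and 27.0 (site 1), 9.0 and 28.5 (site 2), 10.5 and 30.0 (site 3). The gap is 19.5 months at each site, or 1.625 years. The facility-only estimator therefore converts a trend into an effect of about 1.62 times the annual change. Declines of 2, 3 or 5 points per year give 3.2, 4.9 or 8.1 points.

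**Step 3: false-positive rate with no true effect.** Sites contribute 5×6/11 + 6×5/11 + 7×4/11 = 8.0 effective quarters. With n_q cases per site-quarter, SE ≈ √(0.244/(8 n_q)). At 135 per site, n_q = 135/12 = 11.25 and SE = √(0.244/90) = 0.052. At 300 it is 0.035 and at 700 it is 0.023. The rate is Φ(b/SE − 1.96) + Φ(−b/SE − 1.96).

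| Cases per site | 2 points/yr | 3 points/yr | 5 points/yr |
|---|---|---|---|
| 135 | 10% | 15–16% | 34–36% |
| 300 | 15–16% | 29–30% | 64–67% |
| 700 | 30–31% | 57–60% | 94–96% |

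The upper figures spread the cases over the 11 analysed quarters and use variance 0.25. A logistic simulation with site effects agrees: 18% and 30% at 3 points, and 35% and 64% at 5 points, for 135 and 300 per site. With period effects in the model the bias is zero and the rate is 5%.

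**Step 4: what a time term leaves on Table 2.** With wash-in removed, months 18–21 are the only period that holds both a control and a report cell: site 3 in adaptation against site 1 with reports.

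- *Quarter effects:* SE about 0.22 at 135 per site, power about 10%. At 700 per site SE is 0.093 to 0.097, power 34 to 36%.
- *Linear trend:* within sites, the squared correlation of exposure with time is 13²/(8 × 26.6) = 0.79, so the SE grows by 1/√0.207 = 2.2. Power is about 25% at 135 per site (SE 0.115) and 84 to 87% at 700 (SE 0.049 to 0.051).

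If education and adaptation months were also dropped from pre, no control cell would coincide with a report cell. A period-adjusted effect could then not be estimated.

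**The case against.** The strongest reply is the interrupted time series. It is named first for the primary outcome, and such an analysis normally fits a trend. A reader might infer that the GLMM overrides it, or that the plan has no protection against trend at all. The documents support neither reading: the two analyses are unranked, and calendar-time models are planned, if only as exploration. The reply still does not cure the defect. The time-series sentence states no trend or slope term, its description of the effects is garbled, and the clinical outcomes have no such analysis.

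The article is condensed, and the GLMM sentence may not list every fixed effect. That is fair, but the article does not stay silent on time. It gives time an exploratory role, and its power figure fits a model without it.

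A reader might also infer that a false-positive result is likely, or take the 700-per-site rates as the expected ones. The article documents no trend in either direction, and the 2,100 figure belongs to the secondary outcomes; the primary calculation uses 135 per site. Nor does it give a basis for a numerical penalty from correlation within site-quarters. That question, and fixed versus random effects for three sites, can be left to an analysis plan.

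The non-randomised design is openly listed as a limit on causal attribution. That softens the omission but does not remove the bias.

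**Conclusion.** The concern stands in this form: calendar time is not committed to the model that measures primary effectiveness, the time series does not clearly supply it, and the stated power corresponds to leaving time out. If the GLMM is applied as written, it is biased by about 1.6 times the annual background change, in the direction of that change. The factor rests on Table 2, an even spread of cases, and education and adaptation counted as pre; dropping those months raises it to about 1.9. The size of any actual bias is unknown because the trend is assumed. The power comparison rests on the assumed wedge layouts, none of which gave 80% with period effects. This should be settled before analysis, since the design is justified by a control of trend that the stated estimator does not use.

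**What to change.** - Name one deciding primary model and include calendar time in it as a fixed term, in a form the Table 2 schedule can support: for example a linear or coarse-period trend, with quarter effects as a sensitivity analysis.
- Show the GLMM without time only as a sensitivity analysis.
- State how the interrupted time series relates to the deciding model, and which phases count as pre.
- Use the same structure for CIED infection, AKI and *C. difficile*.
- Restate the power under the chosen model and the real schedule.

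The text change is small, but the consequence is not. The interval widens and the stated power falls: at 135 per site to about 10% with quarter effects or 25% with a linear trend, and at 700 per site to about 34–36% or 84–87%. A linear trend buys that precision by assuming linearity, which should be said openly. The primary analysis would probably need all available procedures, well beyond 135 per site.
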